### Additional consent provisions for collection and use of participant data and biological specimens {26b}

This is not applicable.

### Interventions

#### Explanation for the choice of comparators {6b}

The comparator will be normal saline (NaCl 0.9%, dose: 1ml/kg). At this dose, NaCl is neutral regarding its interaction with the coagulation factors and therefore considered a placebo.

#### Intervention description {11a}

Within 1 h of admission, patients are randomized in two arms. In the placebo arm, patients are managed following standard care in addition to intravenous 1ml/kg saline solution. In the treatment arm, patients are managed following standard care in addition to intravenous administration of 1ml/kg four-factor PCC (25 IU/ml of Factor IX/kg). Treatments are given as soon as possible using syringe pumps (120 mL/h).

All centers follow European guidelines for the management of post-traumatic hemorrhage. Details of standard management are found below (11d).

#### Criteria for discontinuing or modifying allocated interventions {11b}

Study treatment is managed by the investigating team, starting within 1-h post-admission and is administered in intravenous perfusion at 2mL per minute. There is no reason for discontinuing or modifying treatment unless an adverse reaction to the study treatment occurs. In this unlikely event, perfusion should be stopped, appropriate care provided immediately, and the event should be reported to the sponsor. Dose change is not permitted by the protocol.

#### Strategies to improve adherence to interventions {11c}

Because the investigating team administrates the treatment, no strategy is needed to improve patient adherence to the intervention.

#### Relevant concomitant care permitted or prohibited during the trial {11d}

From admission, all patients are managed according to European recommendations. Briefly, the source of bleeding should be identified as soon as possible and treated with emergency surgery and/or embolization following standard practice [16]. Regarding resuscitation, patients are treated in both groups with restricted volume replacement strategy, early transfusion of blood products with a RBC:FFP ratio between 1:1 and 2:1. Tranexamic acid (TXA) is intravenously administered within 3h after injury at a loading dose of 1 g infused over 10 min followed by an intravenous infusion of 1 g over 8 h [17]. Fibrinogen concentrate is administered in case of fibrinogen concentration <1.5 g/L [18] or viscoelastic evidence of a functional fibrinogen deficiency [19]. Platelets are administered to maintain a platelet count above 50 x 10^9^/L. Vasopressors can be infused in addition to fluids to maintain target systolic arterial blood pressure (>90 mmHg or >110 mmHg for head-injured patients). Blood samples are regularly drawn from admission to test hemostasis (prothrombin time ratio, Quick time, fibrinogen concentration, and viscoelastic tests where available), blood electrolytes, hepatic and renal function, and blood gases.

#### Provisions for post-trial care {30}

Post-trial care is not planned. Patients who suffer harm from trial participation will be cared for in the intensive care unit. Should prejudice linked to study participation occur, financial compensation will be provided by the insurance (Société Hospitalière d’Assurances Mutuelles—SHAM, [name]) contracted by the promotor.

#### Outcomes {12}

The primary outcome is the total number of blood products transfused within the first 24 h after hospital admission, including RBC, FFP, and platelets. The choice of this primary outcome is based on the following rationale. First, a recent randomized control trial exploring the effect of vasopressin use after severe trauma on the same endpoint [20], Second, even if transfusion is considered a pillar in the management of acute bleeding, blood products are associated with adverse events and poor clinical outcome [11, 21]. Third, mortality after severe trauma is a complex process depending on hemorrhage but also on traumatic brain injury and pre-existing medical conditions, specifically in elderly patients [22]. We thus believe that 24h total blood consumption is an accurate proxy of the severity of the bleeding until the hemorrhage stops.

Secondary outcome measures are (1) number of separate units (and volume) of RBC, FFP, and platelets and transfused in the first 24 h; (2) time to achieve prothrombin time ratio < 1.5; (3) time to hemostasis, defined as the time necessary to control bleeding in the surgical field (operative field is dry without further foreseeable homeostatic procedures) or to control contrast blush after embolization during an interventional radiology (no more dye flushing); (4) number of thrombo-embolic events at 28 days; (5) mortality at 24 h and 28 days; (6) intensive care unit (ICU)-free days (number of in-hospital days outside ICU) within the first 28 days; (7) ventilator-free days during ICU stay within the first 28 days; (8) hospital-free days within the first 28 days; (9) hospitalization status at day 28; (10) GOSE for patients with brain lesions on initial scan; and (11) cost of each strategy at days 8 and 28. Cost analyses will be performed on expensive care: blood products and procoagulant treatments administered, imaging exams, surgeries, and length of stay in each healthcare unit.

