### Eligibility criteria {10}

#### Inclusion criteria

All consecutively admitted adult patients at risk of massive transfusion after severe trauma are screened for enrolment. Patients older than 18 years, admitted directly from the injury scene to a level-I trauma center, are eligible provided that they have two criteria: (1) a transfusion of at least one unit (U) of RBC prior to hospital admission or within the first hour after their admission (a delay of 90 min is tolerated if transfusion is decided within 1 h post admission) and (2) prediction by an assessment of blood consumption (ABC) score ≥ 2 [14] or by physician judgment of the need for a massive transfusion (defined by a transfusion of at least 10 RBC during the first 24 h or 3 RBC during the first hour).

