#### Participant timeline {13}

All consecutive trauma patients admitted directly from the injury scene who require RBC transfusion with a risk of massive transfusion are screened on admission. Eligible patients are then rapidly enrolled by the study investigator. They should be randomized and treated accordingly within 60 min post-admission. After patient treatment, follow-up includes hourly visits until 6 h post-admission, as well as visits at 12 and 24 h to measure prothrombin ratio, assess hemorrhage control and monitor adverse events. Thrombo-embolic events are under special scrutiny during the entire hospital stay because they are frequently expected adverse effects of PCC treatment. Each suspicious thrombo-embolic event should be confirmed with venous Doppler echography or angiography and treated following standard practice. Thromboprophylaxis is left to physician discretion. Patients are followed for 28 days with the last visit aiming at collecting the Glasgow outcome scale extended (GOSE) for patients with brain lesions on initial cerebral imaging, mortality, and place of living (Fig. 1).

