##### Analysis of the main outcome

The main outcome is the total blood consumption (RBC, FFP, and platelets). It will be analyzed after verification that the time spent in the study up to H24 is not significantly different between the two groups. If this duration is not different, the total number of units transfused over 24 h between the two groups will be compared using a bilateral student intent to treat *t* test (if the application conditions are not met, we will use a non-parametric Mann-Whitney *U* test). If the duration is different, the amount of blood products used per hour between the two groups will be compared using an intention-to-treat Student *t* test (= total number of bags transfused over 24 h divided by the time spent in research during the first 24 h), in order to control for an attrition bias created by patients who died before 24 h.

The per-protocol analysis will be performed on patients who actually received treatment within 1 h of admission to the hospital.

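### The primary test ignores units transfused before randomisation; the unit difference is not biased, but precision is given up

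*Protocol article*

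**What the plan says.** Outcomes {12} of the protocol article: "The primary outcome is the total number of blood products transfused within the first 24 h after hospital admission, including RBC, FFP, and platelets". The clock starts at admission.

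Participant timeline {13} on allocation and treatment: "They should be randomized and treated accordingly within 60 min post-admission". Concomitant care {11d} has early transfusion as part of standard management from admission in both arms, so transfusion can run before allocation.

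Inclusion criteria require "a transfusion of at least one unit (U) of RBC prior to hospital admission or within the first hour after their admission", with the tolerance that "a delay of 90 min is tolerated if transfusion is decided within 1 h post admission". One of the two definitions of massive transfusion there is 3 RBC in the first hour, so sizeable early use is foreseen in some patients.

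Analysis of the main outcome: "the total number of units transfused over 24 h between the two groups will be compared using a bilateral student intent to treat" t test, with Mann-Whitney if its conditions are not met. If time in study differs between arms, units per hour are compared by t test. None of these branches has a covariate. Sequence generation {16a} stratifies by centre only, so the design does not balance units already given either.

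**The concern.** Units given between admission and randomisation are in the endpoint but cannot respond to the allocated treatment. How many a patient has had by then probably also indicates how severely that patient is bleeding, and so how many more will follow. An unadjusted comparison leaves both sources of variation in the error term, although the count is fixed before allocation and can safely be conditioned on. At stake is the efficiency of a trial planned at 80% power. Validity is not at stake.

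**Working it through.** **Inputs from Sample size {14}.** 12 versus 9 units on the 24-h total (difference 3), two-sided alpha 0.05, 80% power, 162 per group. No SD is stated. The article gives neither the number of units before randomisation nor their correlation with the total, so those are assumed below.

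**Step 1: the plan's own figure.** Without an SD, 162 cannot be reproduced independently, so I solve backwards with the normal approximation, n = 2·SD²·(1.960 + 0.842)²/3². With n = 162:

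SD = 3 / (√(2/162) × 2.802) = 3 / (0.1111 × 2.802) ≈ 9.64.

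Under Mann-Whitney the implied SD is about 9.4 (relative efficiency 0.955) or 9.0 (0.864).

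**Step 2: expected difference.** Write the total as units before randomisation plus units after. The first part has the same mean in both arms, so it cancels from the expected difference. The 12 and 9 are set on the whole 24-h count, so the planned 80% already includes early units.

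**Step 3: precision.** Let r be the correlation between units before randomisation and the 24-h total. Adjustment reduces the residual SD to SD·√(1 − r²), and

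power = Φ(2.802/√(1 − r²) − 1.960).

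The back-solved SD cancels, so under this approximation the gain depends only on r.

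| r (assumed) | √(1 − r²) | 2.802/√(1 − r²) | Power at 3 units |
|---|---|---|---|
| 0 | 1.000 | 2.802 | 80% |
| 0.3 | 0.954 | 2.937 | 84% |
| 0.4 | 0.917 | 3.057 | 86% |
| 0.5 | 0.866 | 3.235 | 90% |

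**Step 4: what r might be.** Hold the total SD at 9.64 and assume an SD of 1, 2 or 3 for units before randomisation.

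- If they are uncorrelated with later units, r = 1/9.64, 2/9.64 or 3/9.64 = 0.10, 0.21 or 0.31. Adjusted power is 80.4%, 81.7% or 83.8%.
- If they correlate 0.3 with later units, the SD of later units is 9.29, 8.85 or 8.30. Then r = (1 + 0.3 × 9.29)/9.64 = 0.39, (2 + 0.3 × 8.85)/9.64 = 0.48 or (3 + 0.3 × 8.30)/9.64 = 0.57. Adjusted power is 86.1%, 89.2% or 92.6%.

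Most of the gain therefore comes from the early count predicting later bleeding. Removing the early units' own variance contributes little. Consistent with this, counting only units after randomisation without adjustment gives 82.8%, 86.3% or 90.2% in the second set, less than adjustment does.

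**The case against.** The strongest reply is that the endpoint and the planned effect share one scale. Sample size {14} takes 12 units from patients meeting the eligibility criteria and justifies 3 units as an absolute difference. On that scale nothing is diluted, and type I error is intact. This stands in full.

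A reader might still infer that early units dilute the effect and push power below 80%. If the drug cut only later units by 25% and 1, 2 or 3 of the 12 came earlier, the difference would be 0.25 × 11, 10 or 9 = 2.75, 2.50 or 2.25 units, and power 73%, 65% or 56%. The protocol does not assume that: its 25% is the ratio of 9 to 12 on the whole count. Adjustment would not restore a smaller difference either. At 2.5 units and r = 0.4, adjusted power is about 72%. Those figures should not be used against the plan.

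The infusion time is also tempting. The drug "is administered in intravenous perfusion at 2mL per minute", so at 1 mL/kg it runs 30 to 50 min for an assumed 60 to 100 kg. But units given during infusion come after randomisation and must not be adjusted for, and nothing in the article says that the drug has no effect until the infusion ends.

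It is also fair to say that few counted units may precede randomisation. The qualifying unit may be pre-hospital, which the endpoint does not count, or may follow study drug under the 90-min tolerance. Treatment is to be given as soon as possible, with 60 min as the limit. This limits the size of the gain and leaves the point standing.

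Finally, an unseen analysis plan may add adjusted analyses. The article itself, however, fixes the primary test, and that test is unadjusted.

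**Conclusion.** The point holds as a loss of precision. The endpoint can include units given before randomisation, and the stated primary test does not use that count. There is no bias in the unit difference and no shortfall against the planned 80%.

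At a true difference of 3 units, adjustment would raise power to about 84% to 90% for an assumed r of 0.3 to 0.5, and by almost nothing if r is near 0.1. The true r cannot be derived from the article. The figures use a normal approximation for a count that the article says is not normally distributed, so they are indicative. The change is worthwhile because it is cheap, but the trial's validity does not depend on it.

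**What to change.** Keep the 24-h total as the primary endpoint. In the analysis of the main outcome, replace the unadjusted test with a comparison adjusted for the number of units given before randomisation: at least RBC, ideally RBC, FFP and platelets, with pre-hospital units included. Name in advance the rank-based or count-model equivalent to be used if the t-test conditions fail. Report units from randomisation to 24 h as a prespecified supportive analysis. Do not adjust for anything given after randomisation.

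The cost is analysis wording, settled before unblinding, plus unit times that can be placed before or after randomisation. First-hour RBC already has to be ascertained for eligibility and for the massive-transfusion subgroup in {20b}. The split at randomisation is an extra item, because the article relies on blood-bank records of total consumption, and issue times only approximate transfusion times. These times need to be clean in the eCRF.

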### Objectives {7}

The primary objective of the PROCOAG study is to test whether the early PCC administration with standard blood products compared with standard care alone allows better control of post-traumatic hemorrhage, echoed by the total number of blood products transfused within the first 24 h after hospital admission.

Secondary objectives are as follows:
To conduct a separate analysis of the primary outcome:
Assessment of RBC consumptionEvaluation of FFP consumptionEvaluation of platelet consumptionTo compare between the two groups:
Time to normalize hemostasis defined by the time to achieve prothrombin time ratio < 1.5Time from admission to hemorrhage control defined during a surgical and/or radiological procedure, defined as the time necessary to control bleeding in the surgical field (operative field is dry without further foreseeable homeostatic procedures) or to control contrast blush after embolization during an interventional radiology (no more dye flushing).Thromboembolic events (pulmonary embolism, deep venous thrombosis)Morbi-mortality: mortality at 24 h and 28 days, intensive care unit (ICU)-free days (number of in-hospital days outside ICU) within the first 28 days, ventilator-free days during ICU stay within the first 28 days, hospital-free days within the first 28 days, and hospitalization status at day 28,Neurological outcome (Glasgow Outcome Scale Extended, GOS-E) for patients with brain lesions on initial scanTo evaluate differences in terms of cost-effectiveness

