##### Calculation of the cost of each of the strategies

An average cost of care will be calculated for each group. Micro-costing and gross-costing methods will be used to reconstitute the cost of the hospital stay. Thus, data on the consumption of care will be collected prospectively throughout the entire length of the stay in intensive care (the number and nature of blood products and drug treatments used, additional examinations performed, and the length of stay in each care unit). In this way, we can calculate an average cost of the resuscitation stay in each group. The cost of the overall stay will be reconstituted using the modified GHM method, and it will be based on hospital cost accounting data (calculated within the framework of the ENC: national scale of costs).

Comparison of the cost of the two strategies: The difference in costs between the groups will be tested by a Student’s test or by a non-parametric test (Mann-Whitney tests) in case of non-Gaussian distribution. The choice of the test will be made with regard to the distribution of costs in each group (Shapiro-Wilk test, on raw data or, if necessary, on transformed data). If the distribution of costs is not Gaussian, the construction of the confidence interval of the average cost will be based on the non-parametric bootstrap method.

Deterministic and probabilistic sensitivity analyses will be performed to test the robustness of our estimates. Multivariate analyses will also be implemented to take into account censoring (death and follow-up time) in our cost analyses.

Mortalities at 24 h and 28 days will be compared between the two groups using the Kaplan-Meier model. Length of stay will be compared with a Student’s *t* test (if the application conditions are not met, we will use a non-parametric test).

The GOSE at 28 days will be compared with a Student’s *t* test (if the application conditions are not met, we will use a non-parametric test). The locations of the patient’s hospitalization at 28 days will be compared between the two groups using the chi^2^ test (when the application conditions of the chi^2^ test are not met, Fisher’s test will be used).

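### ICU-free and ventilator-free days are defined with restrictions that let a slower recovery score higher than a faster one

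*Protocol article*

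**What the plan says.** Outcomes {12} gives, as secondary outcomes 6 and 7, "intensive care unit (ICU)-free days (number of in-hospital days outside ICU) within the first 28 days; (7) ventilator-free days during ICU stay", the second also limited to 28 days. Objectives {7} carries the same two restrictions: "intensive care unit (ICU)-free days (number of in-hospital days outside ICU) within the first 28 days, ventilator-free days during ICU stay". Outcome 8 is "hospital-free days within the first 28 days", with no further definition. The Abstract names all three free-day outcomes over 28 days without either restriction.

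The analysis sections name no test for the free-day outcomes. The closing paragraphs under the cost heading, next to the mortality and GOSE analyses, state: "Length of stay will be compared with a" t test, or a non-parametric test if its conditions are not met. The Discussion says that the strategy could lower morbidity, as reflected in time in the ICU and time on mechanical ventilation.

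**The concern.** A free-day outcome is meant to rise as the patient does better. The parenthesis in the ICU definition turns it into a count of ward days, so going home early lowers the score. The limit on ventilator-free days turns that outcome into ICU days spent off the ventilator, so staying longer in the ICU after extubation raises the score. A patient can also collect ward days, or unventilated ICU days, and then die.

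The Discussion looks to ICU stay and ventilation for evidence of reduced morbidity. With these definitions, a between-group difference in either outcome has no clear direction: a lower mean could reflect earlier discharge, and a higher mean could reflect longer stays.

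**Working it through.** The article states no figure for these outcomes, so there is none to reproduce. The check applies the written definitions to hypothetical patients.

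**Inputs.** The definitions come from Objectives {7} and Outcomes {12}, with a 28-day window. Let I = ICU days, V = ventilated days, and H = days in hospital until discharge, death or day 28. Assume one ICU stay, ventilation only in the ICU, and elapsed days.

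- As written: ICU-free = H − I; ventilator-free = I − V.
- Comparator (a convention used here for comparison, not taken from the article): 28 − I and 28 − V, with death by day 28 scored 0.

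**Step 1, ICU-free days, both patients with I = 3.** Home on day 10: 10 − 3 = 7. On the ward at day 28: 28 − 3 = 25. The slower recovery scores 25 − 7 = 18 days more. The comparator gives both 28 − 3 = 25.

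**Step 2, ventilator-free days, both patients with V = 2.** ICU discharge on day 3: 3 − 2 = 1. On day 20: 20 − 2 = 18. The longer ICU stay scores 18 − 1 = 17 days more. The comparator gives both 28 − 2 = 26.

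**Step 3, consistency with hospital-free days.** For a patient alive at day 28, ICU days + ward days + days out of hospital = 28. So ICU-free days as written = 28 − I − hospital-free days. With I fixed, each day of earlier discharge adds one hospital-free day and removes one ICU-free day. In step 1 the patient home on day 10 has 18 hospital-free and 7 ICU-free days; the ward patient has 0 and 25. Two outcomes that should both mark benefit move in opposite directions.

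**Step 4, a wider set of patients** (each pair is ICU-free, ventilator-free):

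| Patient | I | V | H | As written | Comparator |
|---|---|---|---|---|---|
| A: home on day 6 | 2 | 1 | 6 | 4, 1 | 26, 27 |
| B: in hospital at day 28 | 10 | 3 | 28 | 18, 7 | 18, 25 |
| C: in hospital at day 28 | 20 | 12 | 28 | 8, 8 | 8, 16 |
| D: ventilated in ICU throughout | 28 | 28 | 28 | 0, 0 | 0, 0 |
| E: dies on the ward on day 25 | 5 | 2 | 25 | 20, 3 | 0, 0 |
| F: dies in ICU on day 15 | 15 | 4 | 15 | 0, 11 | 0, 0 |
| G: dies ventilated in ICU on day 1 | 1 | 1 | 1 | 0, 0 | 0, 0 |

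As written, A, the mildest course, ranks below B and C on both outcomes. A also ranks below E, who dies, on both, and below F, who dies, on ventilator-free days. D and G score 0, as they should.

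**Step 5, direction.** With H fixed, one ICU day fewer raises H − I by one, which is correct. With I fixed, one ventilated day fewer raises I − V by one, also correct. The order fails when H shortens by more than I, or when I lengthens with V unchanged.

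**The case against.** Several arguments on the other side limit the point.

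- **The scale is not reversed.** A reader might infer that a worse course generally scores higher, or that any shortening of stay by PCC lowers these outcomes. Step 5 and patients D and G show otherwise. This objection stands: a worse course can score higher, but need not.
- **Other outcomes would show the truth.** A reader might infer that a benefit would be reported as harm, or early deaths as benefit. Hospital-free days, hospitalization status at day 28, and mortality at 24 h and 28 days are listed alongside and would expose earlier discharge or excess deaths. This stands against the strong reading. It does not make the two affected outcomes interpretable.
- **The value given to deaths and the test for free days may be in the full protocol or the analysis plan.** This largely stands, and neither gap is a finding by itself. Deaths matter here because the written definitions already credit days to patients who later die.
- **Length of stay as a substitute.** A reader might infer that the length-of-stay test replaces the free-day outcomes. The article does not say so. Length of stay is also a cost component, and the Discussion names ICU stay as a marker of morbidity. What remains is that it is a different variable, and that early death shortens it.
- **The wording may be loose,** since the Abstract omits both restrictions. That is possible, but the same restrictions appear in both Objectives and Outcomes, so a single slip is unlikely.

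**Conclusion.** The two definitions are wrong as written. Followed literally, they can place a slower recovery 18 ICU-free days or 17 ventilator-free days above a faster one with the same ICU or ventilator exposure, and can place some deaths above quick survivors. They also set ICU-free days against hospital-free days whenever discharge timing differs with ICU time fixed.

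The sizes come from hypothetical patients and a literal reading. They show that misordering is possible; they do not estimate how often it would occur or which arm it would favour. The documents do not support saying that a PCC effect would be reported with the wrong sign.

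These are two of eleven listed secondary outcomes. The primary analysis and the sample size do not depend on them. The point should be fixed but does not threaten the trial's main conclusion.

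**What to change.** In Objectives and Outcomes, delete the in-hospital restriction from ICU-free days and the ICU-stay restriction from ventilator-free days. Define each as the number of days alive and outside the ICU, or off the ventilator, up to day 28, wherever the patient is. State the value for patients who die by day 28 (conventionally 0), and apply the same rule to hospital-free days so that the three outcomes agree. Analyse these variables themselves in all randomised patients. Read any length-of-stay comparison as descriptive, beside mortality, because early death shortens it.

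The cost is wording in the protocol and analysis plan, settled before unblinding. The admission, discharge, ventilation and death dates are already needed for the listed outcomes, and patients are already followed to day 28.
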